**Fig. 2 Fig2:**
[figure not shown]
Interactive systems framework and stages of the implementation study

#### Aim 1

Refine strategies I (training) and II (TIER) using semi-structured interviews with stakeholders—parent advocates, multidisciplinary health care providers, national pediatric oncology professional organizations, and health care industry leaders (implementation team).

#### Aim 2

Compare the two theoretically based and empirically informed strategies to implement the PAT in English and Spanish using a cluster-randomized controlled trial. Compared to training:

**H2.1**. At the patient/family level, TIER will be associated with: (a) a higher proportion of families of newly diagnosed children screened and provided with feedback (penetration) and (b) higher rates of screening for ethnic minority and socioeconomically diverse families (health equity).

**H2.2**. At the provider level, TIER will be (a) more feasible and rated as appropriate and acceptable, (b) associated with greater engagement in addressing health disparities, and (c) associated with less burnout and better job satisfaction.

**H2.3**. At the institution level, TIER will be associated with: (a) a higher rate of site participation (adoption), (b) more positive perceptions of implementation benefits and fewer challenges (sustainability), and (c) psychosocial care better matched to need demonstrating a more equitable distribution of services and costs of care.

#### Aim 3

Based on the results of the trial and further guidance from the implementation team, we will integrate acceptable, feasible, and effective strategies to develop and disseminate a web-based PAT Implementation Toolkit.

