### Cluster-randomized comparative effectiveness trial (aim 2)

PAT implementation will be tested using a head-to-head randomized implementation (comparative effectiveness of two implementation strategies) trial initiated in three cohorts of 1 year each (2021, 2022, 2023). All 18 pediatric cancer programs invited to participate in the trial agreed to a 2-step randomization process stratified by size of site; sites will be randomized to one of three cohorts and then to strategy, comparing strategy I (training) with strategy II (TIER).

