The outcomes at the institution level (Hyp 2.3) are as follows: adoption, the intention of sites to use the PAT (the ratio of sites that initiate the study); whether screening is perceived as an asset to the institution using the PAT Implementation Questionnaire (PIQ) [35] which will be completed by the site PI, the screeners, and the champion at T1, T2, and T3; whether services are matched to the needs of families based on PPPHM levels using EHR data using the Psychosocial Services and Medical Treatment Checklist (PSMTC) [18] at 30, 60, and 90 days; cost using the data from the PSMTC to estimate the amount of psychosocial staff time and national median hourly salary data [51–53]. The Intensity of Treatment Rating Scale (ITR-3) [54] will be completed at the 90-day post-screening data collection time point based on diagnosis, stage, and treatment.

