H2.1. ANOVA will compare the effectiveness of the two implementation strategies on penetration and health equity. The outcomes are proportions: families screened/families eligible, families provided feedback/families screened, ethnic minority families screened/ethnic minority families eligible, low SES families screened/low SES families eligible. ICCs among the clusters will be calculated and used to adjust for the cluster effect [67, 68].H2.2. Three sets of outcome variables—perception of implementation, engagement in addressing health disparities, and burnout/job satisfaction—will be tested. A two group analysis using Structural Equation Modeling (SEM) will compare the effectiveness of the two strategies [69, 70]. To test the effect of time, we will conduct latent growth curve analysis [71–73]. Analyses will be conducted using Mplus 5.0 [74] with ML estimation for outcome variables that meet the distribution assumptions, and WLSMV estimation for variables that do not. Potential mediating effects of favorable perception of implementation on provider job satisfaction and burnout will be examined using mediation models. TIER is expected to be associated with more favorable perceptions of implementation, less burnout, and higher job satisfaction.H2.3. At the institution level, adoption of the PAT will be measured by a ratio of sites that initiate implementation/sites that agreed (H2.3a). If substitutions are necessary, sites that are newly invited will be added to the denominator and adoption calculated by total acceptances/total invited. ANOVA will be conducted to compare the effectiveness of the two strategies. For H2.3b sustainability (PIQ perceptions of implementation benefits and challenges), ANOVA will be conducted to compare the effectiveness of the two strategies on benefits and challenges. For H2.3c, we are interested in the extent to which psychosocial care is matched to need. A cost-effectiveness threshold or criterion to which to compare costs of screening with these two implementation strategies has not been established, necessitating our consideration of valued outcomes in the psychosocial screening literature and resources available. We will use a data analytic approach that we used previously [18]. ANOVA will be conducted to test whether psychosocial care is matched with levels of psychosocial risks, resulting in a 2 (strategy) × 3 (psychosocial risks: clinical, targeted, universal) design on equitable distribution of services and costs of care. It is expected that the 3 PPPHM levels will be related to number and costs of services provided as measured on the PSMTC, with least at universal and most at clinical. It is expected that TIER will result in a better match between level of risk and services provided. Scores from the PSMTC will be derived and mapped onto the levels of the PPPHM. Additional analyses will be conducted to compare English speaking and Spanish speaking families, different ethnicity, race, and SES and insurance status on the outcome variables for H2.3c.

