## Discussion

Family psychosocial screening, a Standard of Care, if implemented consistently and across children’s cancer programs can reduce disparities in care by facilitating care matched to need, and promote adaptation. The aim of this research is to implement universal, systematic family psychosocial risk screening with the PAT in English and Spanish to assure that *all* families of children newly diagnosed with cancer at the participating cancer centers are screened. Guided by the ISF for Dissemination and Implementation [36], this study will result in the development and broad dissemination of a PAT Implementation Toolkit for successful and sustainable implementation of universal, comprehensive, evidence-based family psychosocial screening for all families in pediatric oncology. As one of the few applications of implementation science in pediatric cancer, the results of this trial will provide valuable information about what strategies are effective in supporting comprehensive care. The broad theory proposed by the ISF is innovative in this field and provides a broad, forward looking approach to the process of advancing integrated care.

This project is ambitious and has some potential challenges. If a site that agreed to participate is unavailable, we have other eligible sites at each size to approach. We will retain the balance of sites from states with health disparity populations if we make substitutions. Second, to focus on population-based implementation, we did not consider sites with fewer than 30 new patients annually, and we selected sites with psychosocial staff at the median or above for their size. In addition, our selection criteria (minority population, psychosocial staff) precluded some sections of the USA, particularly less populated states with the smallest centers. Thus, we will not be able to generalize implementation to the smallest sites with fewer resources. However, we will distribute the PAT Implementation Toolkit to these sites and seek to evaluate the impact of broader dissemination of the Toolkit across sites of different sizes and different geographic locations. Finally, for cost-effectiveness, measuring the cost of psychosocial care is complicated and largely without precedent. Involvement of healthcare leaders in aims 1 and 3 will provide expert input in larger system level change to support family psychosocial risk screening and psychosocial care in pediatric cancer.

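### After any site substitution, adoption (H2.3a) changes from sites that initiate to sites that accept an invitation, which can hide or dilute failures to start

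*Protocol article*

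**What the plan says.** All of the text is in the Protocol article.

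- **Hypothesis (Specific aims, Aim 2, H2.3).** Compared with training alone, TIER is expected to show "a higher rate of site participation (adoption").
- **Outcome (Measurement/outcomes, institution level).** The measure is "adoption, the intention of sites to use the PAT (the ratio of sites that initiate the study"). It mentions no alternative ratio.
- **Analysis (Data analysis, Aim 2, H2.3).** The default is that "adoption of the PAT will be measured by a ratio of sites that initiate implementation/sites that agreed (H2.3a"). The text then continues: "If substitutions are necessary, sites that are newly invited will be added to the denominator and adoption calculated by total acceptances/total invited". For the comparison by arm, "ANOVA will be conducted to compare the effectiveness of the two strategies".
- **Recruitment (Cluster-randomized comparative effectiveness trial).** "All 18 pediatric cancer programs invited to participate in the trial agreed to a 2-step randomization process"; the randomization itself is still to come.
- **Substitution (Discussion).** "If a site that agreed to participate is unavailable, we have other eligible sites at each size to approach". No timing is given.

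**The concern.** H2.3a is a claim about the effect of a randomized strategy, so its outcome should be something a site does after allocation, defined in one way. The plan holds two definitions and lets an event in the conduct of the trial choose between them. That event, an agreed site becoming unavailable and being replaced, is closely tied to what adoption is meant to record.

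The fallback also counts a different behaviour. Accepting an invitation to join a study is not the same as starting to screen families. For the 18 original sites, acceptance was complete before allocation.

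At stake is whether a reported adoption rate, and the difference between strategies, means what the reader will take it to mean. If one arm loses sites and the other does not, the fallback can shrink or remove the difference that H2.3a sets out to detect.

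**Working it through.** **Inputs.** Six sites in each of three size strata (Selection of sites); 9 sites per strategy (Sample size, under Data analysis, Aim 2); 18 of 18 invited sites agreed. The number of substitutions is not given, so it is varied here as an assumption.

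**Plan's own figure.** 6 × 3 = 18 sites, and 18/2 = 9 per strategy, which reproduces the stated group size. The protocol gives no expected adoption rate, effect size or power for H2.3a.

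**Ratios.** In one arm, let *d* of the 9 agreed sites never start. Each is replaced by a substitute that accepts at first approach.

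- A, default definition: (9 − d)/9.
- B, fallback, a lost site still counted as an acceptance: (9 + d)/(9 + d).
- C, fallback, a lost site no longer counted as an acceptance: 9/(9 + d).

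| d | A | C | B |
|---|---|---|---|
| 1 | 8/9 = 88.9% | 9/10 = 90.0% | 10/10 = 100% |
| 2 | 7/9 = 77.8% | 9/11 = 81.8% | 11/11 = 100% |
| 3 | 6/9 = 66.7% | 9/12 = 75.0% | 12/12 = 100% |
| 5 | 4/9 = 44.4% | 9/14 = 64.3% | 14/14 = 100% |

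At d = 2 the fallback raises adoption by 81.8 − 77.8 = 4.0 points under C and by 100 − 77.8 = 22.2 points under B.

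**Difference between arms.** Suppose d = 3 in strategy I and no losses in TIER (9/9). The difference is 33.3 points under A, 25.0 under C and 0 under B. Under B the ratio falls below 100% only if an approached substitute refuses. With three losses and one refusal it is 12/13 = 92.3%.

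**Original sites alone.** Acceptances over invitations is 18/18 = 100% before allocation, whatever happens afterwards.

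**Test.** Adoption is one yes/no value per site, 9 v 9. If every site adopts, the between-arm and within-arm sums of squares are both zero and F is 0/0. One-sided Fisher exact probabilities on the default ratio, against 9/9 in the other arm:

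- 7/9: C(9,2)/C(18,2) = 36/153 = .235
- 6/9: C(9,3)/C(18,3) = 84/816 = .103
- 5/9: C(9,4)/C(18,4) = 126/3060 = .041

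So an exact one-sided test at .05 needs about 9/9 v 5/9. The one-sided .05 level is the one the protocol uses for its patient-level sample size; it states none for H2.3a.

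**The case against.** The best defence is that the term for total acceptances is undefined and can be read kindly. Adding newly invited sites to the denominator suggests that a lost site is meant to stay there and pull the ratio down. On that reading the two-loss example gives 82% against 78%, a modest dilution. This stands. A reader might infer that the rule erases drop-outs and would report full adoption. The text supports only that it could, under the other reading.

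A reader might also infer that adoption under the fallback cannot depend on strategy at all. That is shown only for the original 18. A substitute approached after allocation might know the strategy of the vacant place, and the protocol does not say.

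Nor do the documents support a flat claim that substitutes break the randomized comparison, because substitution is not dated. A site replaced before allocation leaves that comparison intact. And the trigger is substitution, not failure as such: a site that fails to start and is not replaced stays under the default ratio.

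The outcomes section does call adoption an intention, which might seem to favour acceptance. But its metric in the same sentence is initiation, and intention expressed before randomization cannot compare strategies.

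Finally, Fisher's test is hardly more informative than ANOVA when all sites adopt (it returns p = 1), and 18 sites limit any test. That is fair. The exact test is the better-behaved choice, but it does not cure the low power.

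**Conclusion.** The rule is wrong as written. It replaces initiation by acceptance once a site is substituted, contrary to the outcome definition elsewhere in the same article. For the original 18 sites the replacement ratio is fixed at 100% before randomization.

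With two losses out of nine, both replaced at first approach, adoption rises from 78% to 82% or to 100%, depending on a term the protocol leaves open. These sizes rest on an assumed number of losses and on ready acceptance by substitutes. With no substitution the problem does not arise, although the article plans for substitution in two places. If substitution follows allocation, the substitutes also lie outside the original randomized comparison; if it precedes allocation, they do not.

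The point is confined to H2.3a. It does not change how penetration, provider or cost outcomes are defined.

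**What to change.** Delete the fallback and use one definition throughout: sites that start PAT screening divided by sites originally randomized to that strategy. Keep a randomized site that is later replaced in the denominator as a non-adopter. Report substitutes, and acceptance of invitations, separately and descriptively.

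Replace ANOVA for this outcome with counts by arm, an exact interval and Fisher's exact test.

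The cost is a change to the outcome wording and to one test, with no new data. Adoption may look slightly less favourable, and the comparison remains low in power, so H2.3a is best read mainly from the counts and interval. How substitute sites are handled for the other hypotheses can be left to the analysis plan.

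### The 2 × 3 ANOVA for H2.3c probably over-rejects under the plan's own expected pattern, and its omnibus interaction has no direction and no stated scale for a better match

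*Protocol article*

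**What the plan says.** The hypothesis (Specific aims, Aim 2, H2.3) is that TIER gives "psychosocial care better matched to need demonstrating a more equitable distribution of services and costs of care".

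The test is in the H2.3c text of Data analysis, Aim 2 (printed under the subheading on data cleaning and missing data): "ANOVA will be conducted to test whether psychosocial care is matched with levels of psychosocial risks". The layout crosses the two strategies with the three risk levels, and the outcomes are the services given and what they cost. Two expectations follow. The first concerns the gradient over the risk levels, which should prove "related to number and costs of services provided as measured on the PSMTC, with least at universal and most at clinical". The second is the comparison of strategies: "It is expected that TIER will result in a better match between level of risk and services provided".

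On the outcome, the text adds that "Scores from the PSMTC will be derived and mapped onto the levels of the PPPHM" and refers to an earlier study's approach. It names no model term as the test of a better match, no scale on which match is measured, and no provision for unequal variances. For H2.2, the same section does give an alternative estimator for variables that fail the distribution assumptions.

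The background section on the PAT describes the three levels as a pyramid: most families are universal, a smaller group is targeted, and clinical is at the top. No percentages, means or SDs are given.

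**The concern.** Three features of the named test bear on whether a significant result would mean what H2.3c says.

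- **Error rate.** ANOVA pools one variance over all six cells. Counts and costs usually vary more where their mean is higher. If the highest-mean level is also the smallest, the pooled variance is dominated by large, low-variance cells and understates the error of the clinical cells.
- **Direction.** The strategy by risk interaction has 2 df. It rejects for any departure from parallel profiles, including one where TIER follows risk less closely.
- **Scale.** On untransformed counts or costs, the interaction null is equal absolute differences between strategies at every level. A uniform percentage increase breaks that null, although the ratio between levels is unchanged.

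A variance artefact, or a general rise in the amount of care, could then be read as care that is better matched and more equitably distributed. The trial results also feed the Toolkit.

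**Working it through.** **Inputs from the plan.** Families: 6 × (60 + 92 + 339) = 6 × 491 = 2946, or 1473 per strategy, which reproduces the stated total. The stated effective size is 950 per arm, and the simulations use it. The mean site size of 2946/18 = 163.7 and ICC .005 would give 1473/(1 + 162.7 × .005) = 812 instead. Step 1 shows that the inflation does not depend on this. No power figure is stated for H2.3c.

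**Assumed inputs.** Mean services 4/6/9 at universal/targeted/clinical; negative binomial counts with size k = 2 or 5; risk shares 65/25/10 or 50/30/20; equal arms; independent families.

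**Step 1: hand check of the variance effect.** The variance in a cell is μ + μ²/k.
- k = 2: 12, 24, 49.5.
- k = 5: 7.2, 13.2, 25.2.

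The pooled variance is the share-weighted mean. Take the clinical-minus-universal difference between strategies. Its true variance is proportional to V_U/s_U + V_C/s_C, and ANOVA uses V_pooled × (1/s_U + 1/s_C). The number of families cancels in the ratio.

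| Shares, k | Pooled variance | True | Used by ANOVA | √(used/true) | Actual two-sided level at nominal 5% |
|---|---|---|---|---|---|
| 65/25/10, 2 | 7.8 + 6.0 + 4.95 = 18.75 | 12/.65 + 49.5/.10 = 513.5 | 18.75 × 11.54 = 216.3 | 0.649 | critical value 1.96 × 0.649 = 1.27, about 20% |
| 50/30/20, 5 | 3.6 + 3.96 + 5.04 = 12.6 | 7.2/.50 + 25.2/.20 = 140.4 | 12.6 × 7 = 88.2 | 0.793 | critical value 1.96 × 0.793 = 1.55, about 12% |

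**Step 2: simulation of the 2-df interaction F test, no strategy effect.** With 950 per arm under the same assumptions it rejects in 10 to 19% of runs. With cell-specific variances the rate is 4 to 6%.

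**Step 3: when the inflation occurs.** Separate runs used equal means in both strategies and 950 per arm:

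| SD pattern (universal:targeted:clinical) | Shares | Rejection |
|---|---|---|
| Equal | 60/30/10 | 4.9% |
| 1:1.5:2 | 60/30/10 | 15.9% |
| 1:1.5:2 | 50/35/15 | 11.6% |
| 1:2:4 | 60/30/10 | 28.8% |
| 1:1.5:2 | equal-sized levels | 5.1% |
| Doubled in TIER only, equal arms | 60/30/10 | 5.1% |
| 2:1.5:1 | 60/30/10 | 1.6% |

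Inflation needs the larger variance in the smaller cells.

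**Step 4: dependence on scale.** If TIER multiplies every mean by 1.5, 4/6/9 becomes 6/9/13.5. The absolute differences are 2, 3 and 4.5, so the additive interaction is non-zero, but clinical/universal stays at 9/4 = 13.5/6 = 2.25. In runs with means 4/6/8 or 3/6/12, coefficient of variation 0.7 and shares 60/30/10 or 50/35/15, a uniform 20% increase makes the pooled interaction test reject 32 to 67% of the time at 950 per arm. With cell-specific variances on the same scale it still rejects 18 to 49%, so a robust variance alone does not settle the scale.

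The reverse also holds. If TIER adds 2 services at every level, 4/6/9 becomes 6/8/11. The absolute differences are equal, but the ratio falls from 2.25 to 11/6 = 1.83. At 950 per arm a contrast of log means then rejects 39 to 84% of the time, in the direction of a worse match under TIER.

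**The case against.** The strongest reply is that this is a condensed article. It never says the outcome is untransformed, it says PSMTC scores will be derived, and it relies on precedent ("We will use a data analytic approach that we used previously [18"]) that is not shown here. Scale, contrast and variance model could be in the full protocol or analysis plan. That stands in part: untransformed is the plain reading of number and costs of services, but it is an inference. The article does, however, fix the method as ANOVA and state the expected gradient, and those two sit badly together.

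A reader might infer from Step 4 that a rejection under a uniform percentage increase is a false positive. The documents do not support that. They do not define match as a ratio, and giving more of the added care to higher-risk families is a legitimate absolute reading. A log-ratio test has the mirror-image problem. The defect is that the scale is open, not that the additive scale is wrong.

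A reader might also infer that any difference in variances inflates the test. Step 3 shows otherwise.

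Nor does the plan say that a risk main effect would count as support for TIER; it states the gradient and the better match as separate expectations. Any omnibus test lacks direction, and the cell means would show it. A single directional contrast is still the closer test of a directional hypothesis.

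**Conclusion.** The point holds as a correctable weakness in the stated test. Under the pattern the plan itself expects, most care at the clinical level and fewer families there, pooled-variance ANOVA probably rejects well above 5% with no strategy effect. The figure is about 10 to 19% under the main assumptions, and up to 29% in the steepest SD pattern tried. More families would not cure this.

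The rates are illustrative. They rest on assumed means, dispersion and risk shares, on reading the outcome as untransformed, and on independent families, although strategy is assigned to 18 sites. They do not describe the trial's exact error rate.

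Separately, the 2-df interaction does not test a direction, and its result depends on a scale that the plan does not fix. It would go too far to call H2.3c the main institution-level conclusion, since H2.3 has three parts and none is ranked first, or to say that a log-link model is required.

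**What to change.** In the H2.3c text of Data analysis, Aim 2:

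1. Replace the pooled-variance ANOVA test by a model with heteroscedasticity-robust variance, clustered by site, with a small-sample correction because there are only 18 sites.
2. Name one 1-df test for each outcome (number, costs): the strategy by ordered-risk contrast from universal to clinical, with TIER steeper than Training as the supporting direction.
3. State before the data are seen whether match means absolute or relative differences between levels, and report the other scale as a sensitivity analysis. A log-link model is one option for the relative scale; for costs it should allow zeros, in case some families have no recorded service.

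The cost is small: a change of wording, the same data and standard software. The downside is slightly wider intervals and one extra sensitivity analysis.

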PAT implementation will be tested using a head-to-head randomized implementation (comparative effectiveness of two implementation strategies) trial in three cohorts over 3 years. *Randomization*. Eighteen sites will be randomized to one of three cohorts. Each cohort will be further randomized to one of the two strategy conditions. Randomization will stratify sites by size to maximize internal validity and statistical power. Sites will be randomized by a data analyst not connected with the study using a two-step Excel = RAND() function. The sequence will be stored in a password-protected electronic file. *Sample size*. The estimated sample of patients/families is based on the median number of new patients each year from the PIPS-CSS database: small (*n* = 60), medium (*n* = 92), large (*n* = 339) multiplied by 6 sites at each size, a total of 2946, with 1473 families allocated to each strategy. With an anticipated Interclass Correlation Coefficient (ICC) [65] of .005, the effective sample size is 950 per arm, a sample size that is sufficient to detect a small effect between the two strategies given 80% power (alpha = .05, one sided). We project a Hispanic sample of 20% of the total (*n* = 589). Based on our research [8], approximately 30% of Hispanic caregivers will be more acculturated/not literate in Spanish at the level necessary to complete the Spanish PAT, rendering a sample of 412. With an anticipated ICC of .005, the effective sample size is 224 which is sufficient to detect a medium effective between the English and Spanish versions given 80% power (alpha = .05, one sided). At the provider level, each of 18 sites has a PI and up to four people screening, and for TIER sites, a champion. Therefore the staff sample ranges from a minimum of 45 ([18 × 2] + 9) to a maximum of 99 ([18 × 5] + 9), likely in the middle given the range of size of sites. At the institution level, 18 sites will be randomly assigned to one of two strategies (9 sites/group). These sample sizes are comparable to other implementation science studies [66].

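### The site-cluster adjustment is stated only for H2.1 and should be extended to H2.2, H2.3b and H2.3c, chiefly for the strategy main effect in H2.3c

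*Protocol article*

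**What the plan says.** The protocol article fixes the design under Data analysis, Aim 2: "18 sites will be randomly assigned to one of two strategies (9 sites/group"). The analysis for each hypothesis follows in the text after the heading on data cleaning and missing data.

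- **H2.1** (penetration, equity): ANOVA on proportions, ending with "ICCs among the clusters will be calculated and used to adjust for the cluster effect".
- **H2.2** (staff measures): "A two group analysis using Structural Equation Modeling (SEM) will compare the effectiveness of the two strategies", with latent growth curves for time and mediation models. No site term is named.
- **H2.3a** (adoption): a ratio of sites.
- **H2.3b** (PAT Implementation Questionnaire, PIQ): "ANOVA will be conducted to compare the effectiveness of the two strategies on benefits and challenges". The measurement section has the site PI, the screeners and the champion all completing the PIQ.
- **H2.3c** (services and costs): "ANOVA will be conducted to test whether psychosocial care is matched with levels of psychosocial risks", in a 2 (strategy) × 3 (risk level) layout. Risk level comes from each family's PAT score.

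The only general statement on covariates is that program size and cohort will be controlled if needed. Site is not mentioned there.

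**The concern.** Families and staff are nested in the units that were randomised. In H2.3c the risk factor is a family attribute, so the natural data rows are families, and a plain two-way ANOVA tests strategy against variation between families. Strategy varies only between sites, so its error must include variation between sites. The site-selection text itself links program size to psychosocial team size and resources, so service counts and costs can be expected to differ by site. Controlling for size and cohort does not remove the remaining differences between sites.

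If site is left out, a cost or service difference caused by which nine sites fell in each arm could be credited to TIER and carried into the Aim 3 toolkit. The same logic applies to H2.2 and H2.3b, with much smaller clusters.

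**Working it through.** **Inputs from the protocol article.** Site sizes: "small (*n* = 60), medium (*n* = 92), large (*n* = 339) multiplied by 6 sites at each size". Families: "a total of 2946, with 1473 families allocated to each strategy". Clustering: "With an anticipated Interclass Correlation Coefficient (ICC) [65] of .005, the effective sample size is 950 per arm". The only alpha given is .05, one-sided. Staff: 45 to 99 in 18 sites, or 2.5 to 5.5 per site.

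**The plan's own figure.** Mean site size is 2946/18 = 163.7.
- Equal sizes: design effect DE = 1 + (163.7 − 1) × .005 = 1.81, so effective n = 1473/1.81 = 812.
- Unequal sizes: DE = 1 + [(1 + CV²) × mean − 1] × ICC. With CV = 0.76, (1 + CV²) × mean = 258.6, so DE = 1 + 257.6 × .005 = 2.29 and effective n = 644.

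The stated 950 is not reproduced; it implies DE = 1473/950 = 1.55. This does not change the power conclusion: taking small as d = 0.2 (assumed), 310 per arm are needed one-sided, and 644 give over 97% power.

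**H2.3c, strategy main effect, site ignored.** The false-positive rate is P(Z > 1.645/√DE) one-sided, or 2 × P(Z > 1.96/√DE) two-sided.

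| Case at ICC .005 | DE | one-sided | two-sided |
|---|---|---|---|
| DE implied by the stated 950 | 1.55 | 9.3% | 11.5% |
| Equal sites | 1.81 | 11.1% | 14.6% |
| Planned unequal sites | 2.29 | 13.8% | 19.5% |
| Unequal, 75% screened (assumed) | 1.96 | 12.0% | 16.2% |
| Unequal, 50% screened (assumed) | 1.64 | 10.0% | 12.6% |

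The last two rows multiply 258.6 by .75 and .50. They are relevant because only a screened family has a risk level. At an assumed ICC of .05 with all families, DE = 13.9 and the rates are 33% and 60%.

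Simulating the 2 × 3 ANOVA under no effect (2000 runs, two-sided 5%, risk shares of 60/30/10% assumed) gave 18.9% at ICC .005 and 61.5% at .05. A t-test on the 18 risk-adjusted site means gave 4.3–4.9% in every scenario.

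**H2.3c, strategy × risk interaction, same simulation.**
- Sites differ only in overall level: 4.5–6.0%, because the contrast is within site.
- Risk gradient also varies by site (all values assumed): 10% with a site-by-risk variance share of .005 at ICC .005; 28% and 50% with shares of .02 and .05 at ICC .05.

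**H2.2 and H2.3b, staff level.** DE = 1 + (k − 1) × ICC for k staff per site.
- ICC .005, k = 2.5 to 5.5: DE = 1.008 to 1.022, giving 5.1–5.2% one-sided.
- Assumed ICC .1, k = 3: DE = 1.2, giving 7.4% two-sided (7.5% simulated).
- Assumed ICC .2, k = 5: DE = 1.8, giving 14.4% two-sided (15.2% simulated).

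**The case against.** The strongest reply is that the article does not say observations will be treated as independent. H2.1 is also called an ANOVA and is nevertheless cluster-adjusted; H2.3 is introduced as institution-level, with nine sites per group; H2.3c refers to a previously used method that is not shown; and a condensed article may leave site terms to an analysis plan. This stands in part: independence is inferred from the named methods. But the article does fix the procedures, factors, software and estimators, and it attaches the adjustment to one hypothesis, so a reader would take it to belong there.

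The institution-level reading does not fully rescue H2.3c. If the 2 × 3 ANOVA were run on 54 site-by-risk means, each site would supply three correlated values. A simulation under no effect (8000 runs per ICC, risk shares 60/30/10% assumed) put the main-effect error at about 7% at ICC .005 and 16–17% at .05, two-sided, while one mean per site held about 5%.

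A reader might also infer that every H2.2 and H2.3 comparison will produce far too many false positives. The documents do not support that:
- H2.3a has sites as its unit.
- Staff clusters are too small for material inflation at the plan's ICC.
- The contrast that H2.3c hypothesises, a closer match of services to risk under TIER, is the interaction. It is inflated only if the gradient varies by site, and the document gives no value for that.

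**Conclusion.** The point holds for H2.2, H2.3b and H2.3c: a site-randomised trial names analyses for them with no allowance for site. The material consequence is the H2.3c strategy main effect on services and costs, where a nominal 5% becomes about 14% one-sided or 19% two-sided if all eligible families are analysed, and about 10–12% one-sided if 50–75% are screened.

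These figures assume that the ANOVA is run on families as written and that the plan's ICC of .005 applies to services and costs; a larger ICC would make them worse. The interaction is at risk only under between-site variation in the gradient (about 10–50% at the assumed values). For H2.2 and H2.3b the omission is one of principle at ICC .005 and becomes moderate, about 7–15% two-sided, at assumed ICCs of .1–.2 with 3–5 staff per site.

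**What to change.** Extend the H2.1 cluster sentence to H2.2, H2.3b and H2.3c, and say how it will be met:

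- **H2.3c:** a random site effect plus a site-by-risk term, with strategy and strategy × risk tested on between-site small-sample degrees of freedom for 18 clusters. Site-level summaries are an acceptable alternative: one risk-adjusted mean per site for the main effect, and one risk gradient per site for the interaction.
- **H2.2:** keep the SEM, growth and mediation models, with site accounted for through a cluster-adjusted or multilevel version and the small number of clusters respected.
- **H2.3b:** a random site effect, or one mean per site, with the same degrees of freedom.
- **H2.3a:** no change on this account.

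The cost is a few sentences in the plan and standard software. No new data are needed. Intervals for strategy effects will be wider, most clearly for services and costs.
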